The secondary endpoints of the study are as follows:Clavien-Dindo grade I–V complications within 30 postoperative daysReoperation rateOperative time (minutes)Length of stay (LOS, days)Quality of life (QoL) measured by the 36-item RAND health survey (RAND-36)Incidence of hernia on long-term follow-up (5 years)

#### Pre-intervention data

BMIASA classificationOther significant diseases and medicationsSmoking historyPrevious hernias, both symptomatic and asymptomatic, operated or unoperatedOperative details on anterior resection, including anastomosis technique, distance from the anus, complications, and problems with the formation of stomaTumor-node-metastasis (TNM) classification of the rectal cancerQuality of life measured by RAND-36 questionnaire

#### Intervention data

Antibiotic prophylaxis usedOperative time, operation room time, time to apply the mesh/implantTechnique and approach used to close the stoma and re-establish intestinal continuity

#### Post-intervention data

Length of hospital stayAll complications measured by the Clavien-Dindo classificationSurgical site infection classified by the CDCDemand for re-operation and mesh removalRe-admissionsRAND-36 questionnaireClinically and/or CT-detectable herniaHemoglobin, carcinoembryonic antigen (CEA)Bowel functionState of incisional wound for loop-ileostomy closure when leaving the hospital

#### Participant timeline

Randomization started in February 2018 at Oulu University Hospital and will last for 2 years. The follow-up schedule is presented in Table 2. Short-term results and complications will be monitored at discharge and 1 month after the operation. CT scans to detect subclinical hernias besides clinical evaluation will be performed 10 months after stoma closure as part of the routine protocol of rectal adenocarcinoma follow-up.

**Table 2 Tab2:** Schedule of events

Schedule of events	Baseline	Procedure	Discharge	30 days ± 3 days	10 months ± 14 days	3 year ± 30 days	5 years± 30 days	Unscheduled visit
Informed consent	X							
Demographics and medical history	X							
QoL	X			X	X	X	X	
Procedure details		X						
CT scan findings					X			
Protocol deviation	X*	X*	X*	X*	X*	X*	X*	X*
Complications		X*	X*	X*	X*	X*	X*	X*
Study exit form							X**	

*Complete if applicable

**Complete when lost to follow-up, consent withdrawal, or when the subject has completed all study-related visits

*CT* computed tomography, *QoL* quality of life

#### Sample size

Two of the previously published retrospective studies reported the incidence of incisional hernias to be 13.5–21.5% on short-term follow-up after closure by suturing [8, 9]. Likewise, the number of hernias after closure with mesh has been very few in short-term follow-up [20, 22]. We assume that the hernia rate after closure by suturing detected in previous studies can be significantly diminished to about 5% with a prophylactic synthetic mesh or biological implant on long-term follow-up. The aim of the study is to generate preliminary results showing synthetic mesh is non-inferior to biological mesh. Assuming α = 0.05 and a power = 80% for incisional hernias and with 5% non-inferiority marginal, we would need 235 patients per group. Although previous studies on both biological implants and synthetic meshes have raised no concerns on the safety of the meshes [18–20, 22, 23], the use of synthetic meshes in contaminated surgical sites continues to be widely avoided in clinical practice, and no comparative studies on incisional hernia prophylaxis after temporary stoma closure exist. That said, we assume there is no difference in infectious complications between the meshes.

As this is a pilot study, each group will comprise 45 patients. Considering a possible 10% drop-out rate, our aim is to have 50 patients per group. Therefore, the estimated sample size of 50 in each group should give a reliable preliminary estimation of the safety and efficiency of both meshes for further studies.

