#### Statistical methods

The main endpoints are the presence (proportion) of stoma site incisional hernias with 95% confidence intervals for both groups at 10-month follow-up, and the incidence of surgical site infection at 30 days after the closure of the stoma. Secondary outcomes are the presence of stoma site incisional hernias at 3- and 5-year follow-up, the relative improvement to QoL during the follow-up, Clavien-Dindo classification of complications at 30 days postoperatively, operation time, length of hospital stay, and reoperation rate.

Between-group comparisons of continuous variables will be performed by Student’s *t* test or Mann-Whitney *U* test, the latter of which will be used if heterogeneous variances persist. Categorical data will be compared using χ^2^ or Fisher’s exact test. Repeatedly measured continuous data will be analyzed by a linear mixed model (LMM) using individuals as random effects. The covariance pattern for the LMM was chosen according to Akaike’s information criteria. Two-tailed *p* values will be reported. Analyses will be performed using SPSS (version 24 or higher) (IBM Corp., Armonk, NY, USA) for Windows and SAS (version 9.4 or higher) (SAS Institute, Cary, NC, USA).

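### With 45 evaluable patients per arm the pilot can estimate the hernia difference only to about ±9 points, so its wording about showing non-inferiority within 5 points and about a reliable estimate needs restating

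*Protocol article*

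**What the plan says.** The Sample size section gives the purpose: "The aim of the study is to generate preliminary results showing synthetic mesh is non-inferior to biological mesh". It assumes that the hernia rate seen after suture closure, quoted as 13.5–21.5%, "can be significantly diminished to about 5% with a prophylactic synthetic mesh or biological implant on long-term follow-up". It then states: "Assuming α = 0.05 and a power = 80% for incisional hernias and with 5% non-inferiority marginal, we would need 235 patients per group".

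The section does not use that number. Because the trial is a pilot, it takes 45 patients per group, raised to 50 for a 10% drop-out, and concludes that "the estimated sample size of 50 in each group should give a reliable preliminary estimation of the safety and efficiency of both meshes". The Objectives section goes further and speaks of demonstrating that the two devices are equal in safety and efficiency.

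The Statistical methods section describes the main hernia result as the proportion of "stoma site incisional hernias with 95% confidence intervals for both groups at 10-month follow-up". Categorical data are compared by chi-square or Fisher's exact test, and "Two-tailed *p* values will be reported". It names no confidence interval for the between-group difference and no non-inferiority test.

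**The concern.** The aim is worded as showing non-inferiority, and the chosen size is called reliable. The size is about a fifth of what the plan itself calculates for that aim (45/235 = 0.19). The pilot label explains why fewer patients are taken. It does not tell the reader what 45 per arm can deliver, and no precision figure supports the word reliable.

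What is at stake is the conclusion drawn at the end. The only between-group tests named for hernia are two-tailed tests of difference. With about two hernias expected per arm, such a test will almost always be non-significant. Beside a stated aim of showing non-inferiority and talk of demonstrating equality, that result could easily be reported as if it supported either.

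**Working it through.** **Inputs.** Hernia rate 5% in both arms; margin 5%, read as absolute percentage points; alpha 0.05 with sidedness not stated; power 80%; 45 evaluable and 50 randomized per group (all from Sample size). Two-tailed p values and per-group 95% intervals (Statistical methods).

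**1. The plan's own figures.**

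n per group = (z_α + z_0.80)² × 2 × 0.05 × 0.95 / 0.05² = (z_α + 0.842)² × 38

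- One-sided 0.05: (1.645 + 0.842)² × 38 = 234.9, so 235. This matches the plan.
- One-sided 0.025: (1.960 + 0.842)² × 38 = 298.3, so 299.
- Drop-out: 45 / 0.90 = 50. This also matches.

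The 235 is therefore right for one-sided alpha 0.05. At one-sided 0.025, 235 per group would have 70% power.

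**2. Power for non-inferiority with 45 per arm.**

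SE = √(2 × 0.05 × 0.95 / 45) = 0.0459; margin/SE = 0.05 / 0.0459 = 1.088; power = Φ(1.088 − z_α)

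| One-sided alpha | 45 per arm | 50 per arm |
|---|---|---|
| 0.05 | 28.9% | 30.9% |
| 0.025 | 19.2% | 20.8% |

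Exact binomial enumeration with 45 per arm gives 21–24% and 12% with score-type limits, and 31% and 21% with Wald limits. The method moves the figure but not the message.

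**3. Precision of the difference, 45 per arm.**

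- 95% half-width: 1.96 × 0.0459 = 0.090, or 9.0 points. This is 9.0 / 5 = 1.8 times the margin.
- 90% half-width: 1.645 × 0.0459 = 0.076, or 7.6 points. This too is wider than the margin.

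**4. Precision within one arm.**

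- Expected hernias: 45 × 0.05 = 2.25.
- Observed 2/45 (4.4%): exact (Clopper-Pearson) 95% interval 0.5% to 15.1%. This includes 13.5%, the lower of the two suture-closure rates that the plan cites.
- Chance of no hernia at all in a given arm: 0.95^45 = 9.9%.

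**5. What the planned test of difference would show.** If synthetic mesh were truly worse by the whole margin (10% against 5%), a two-sided Fisher test at the 0.05 level with 45 per arm would be significant in only about 6% of trials. A non-significant result therefore says almost nothing about the margin.

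**The case against.** The strongest reply is that the plan hides nothing. It prints the powered size directly before the size it uses, and calls the trial a pilot or its results preliminary in the Abstract, Objectives, Sample size and Discussion. It promises only a preliminary estimate for further studies. This stands: low power in a declared pilot is a conceded limitation. A reader might infer that the plan calls 50 per group reliable for a non-inferiority conclusion, but the text does not say so.

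The 235 is also not an arithmetic error. Only its sidedness is unstated. The planned 95% intervals are for each arm's proportion, and the two-tailed p values follow a list of tests of difference. Neither fixes the level of a non-inferiority test, so the plan does not commit itself to 299. Nor does either number size this trial.

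A reader might further infer that 45 per arm could not meet the margin even with no hernia in either arm. That depends on the interval, and the plan names none for the difference. For 0/45 against 0/45 at one-sided 0.05, the upper limit is 5.7 points by Newcombe, Farrington-Manning and Miettinen-Nurminen, but 4.9 by Agresti-Caffo, and the Wald interval has zero width. At one-sided 0.025 the score-type limits are 7.9 points and Agresti-Caffo gives 5.8. Unequal counts can also pass: by score-type limits, 0 hernias with synthetic against 1 with biological meets the margin at one-sided 0.05, and 0 against 2 at one-sided 0.025. The margin is hard to reach, not out of reach.

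What the reply does not remove is the wording. Disclosing a small size does not make showing, demonstrating or reliable accurate.

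**Conclusion.** The point holds as one about claims and interpretation, not about arithmetic or the choice of sample size. At the plan's own assumptions, 45 evaluable per arm gives about 19–29% power for non-inferiority, depending on sidedness. The 95% half-width for the difference is about 9 points against a 5-point margin, and the upper limit for one arm is near 15%. That does not support an aim of showing non-inferiority, talk of demonstrating equality, or the word reliable without figures.

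Two secondary points need a clarifying line. The alpha behind 235 should be stated as one-sided 0.05. The 5% is described as a long-term rate, while the main hernia endpoint is at 10 months and the Background says that incidence rises with time.

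The figures assume a true 5% rate in both arms, an absolute margin and 10% drop-out. They concern hernia only. The plan gives no assumed infection rate, so precision for the other main endpoint is not quantified here. The matter is worth correcting because it changes what the trial may conclude, but its weight is moderate: the shortfall is disclosed and the design can stay as it is.

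**What to change.** Keep 50 per group and change the text.

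1. In Objectives and Sample size, replace the language of showing non-inferiority and demonstrating equality with estimating the between-group difference in hernia at 10 months, reported with its confidence interval. Name that interval in Statistical methods.
2. State that the pilot is not sized to confirm the 5-point margin, and that a non-significant two-tailed test will not be read as non-inferiority or equality.
3. Replace the word reliable with the expected precision: about ±9 points (95%) for the hernia difference, and an upper 95% limit near 15% for one arm with 2/45.
4. State that 235 per group is for one-sided alpha 0.05, and that one-sided 0.025 would need 299.
5. Say which time point the 5% refers to.

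The cost is wording in three sections and a less favourable statement of what the trial can show. It needs no extra patients, visits or data.

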#### Recruitment

All subjects fulfilling the inclusion criteria at each research site will be considered to participate in the trial at 1-month follow-up after anterior resection. An anonymous record will be kept prospectively on all subjects fulfilling the inclusion criteria but not attending, either by declining or for any other reason, for later assessment of selection bias.

### Assignment of interventions

#### Allocation

Subjects will be randomly allocated to study groups according to a computer-generated list compiled by a biostatistician otherwise uninvolved in the clinical care of trial patients.

Randomization will be performed in blocks, where the block size will vary randomly between two, four, and six. A separate randomization list will be created for each center, and randomization will be accomplished by electronic software. Randomization will be performed after confirmation of patient eligibility and willingness to participate.

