## Methods

### Study setting

This study will be completed in several university and central hospitals in Finland: Oulu University Hospital, Turku University Hospital, Tampere University Hospital, Kuopio University Hospital, Jyväskylä Central Hospital, and Seinäjoki Central Hospital.

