#### Exclusion criteria

Presence of a comorbid illness or condition that would preclude surgical treatment (American Society of Anesthesiologists [ASA] grade 4–5).Concurrent or previous malignant tumors within 5 years before study enrollmentPresence of T4b tumors necessitating a multi-organ resectionPatients treated with postoperative adjuvant chemotherapyPatients undergoing emergency proceduresPrimary rectal surgery along with major concomitant procedures (e.g. hepatectomies, other intestinal resections).Metastatic disease with life expectancy of less than 12 monthsPregnancy or suspected pregnancy

All subjects who have had anterior resection and TME for rectal adenocarcinoma at any of the study sites and have not received any adjuvant oncological treatment due to routine protocol of rectal cancer treatment will be considered for inclusion at 1-month follow-up at the outpatient department after the primary operation. The current practice at Oulu University Hospital is to close temporary loop ileostomy by suturing the fascial defect without a mesh at either 2–4 months after uncomplicated anterior resection or about 8–12 months after anterior resection after adjuvant oncological treatment has been accomplished. A full-body CT scan is part of the 1-year follow-up protocol after anterior resection for rectal adenocarcinoma. Therefore, only subjects not receiving adjuvant treatment can be enrolled in the study without having any additional radiation and still undergo a CT scan for both cancer follow-up and detection of possible incisional hernias about 1 year from each operation. After receiving proper information on the possible advantages and disadvantages of intervention, and after voluntarily signing the informed consent form, the subjects will be enrolled in the Preloop trial.

Participating investigators are qualified colorectal or general surgeons experienced in the surgical management of patients with temporary stomas. Further, all participating surgeons are experienced in the relevant technique for loop-ileostomy closure procedures and the use of retromuscular meshes. The technique that will be used to apply both the synthetic mesh and the biological implant is identical. Surgeon contributions to the study will be limited to no less than 10 cases per hospital, and all attending hospitals will be directed to assign the operations to specific surgeons to eliminate potential sources of bias.

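### Randomisation is stratified by centre but the named between-group tests have no centre term: a minor loss of precision if centre predicts outcome, mainly for operating time and length of stay

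*Protocol article*

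**What the plan says.** The protocol article's Allocation section states: "A separate randomization list will be created for each center". It adds: "Randomization will be performed in blocks, where the block size will vary randomly between two, four, and six". Study setting names six hospitals: "Oulu University Hospital, Turku University Hospital, Tampere University Hospital, Kuopio University Hospital, Jyväskylä Central Hospital, and Seinäjoki Central Hospital". The text under Exclusion criteria sets a minimum volume, "Surgeon contributions to the study will be limited to no less than 10 cases per hospital", and tells hospitals to give the operations to particular surgeons.

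Statistical methods assigns Student's t or the Mann-Whitney U test to continuous outcomes. For binary outcomes, which include both main endpoints, it says: "Categorical data will be compared using χ^2^ or Fisher’s exact test". For repeated measures: "Repeatedly measured continuous data will be analyzed by a linear mixed model (LMM) using individuals as random effects". The fixed effects of that model are not listed. No method named in the section mentions centre, and no reason is given for leaving it out.

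**The concern.** Separate blocked lists keep the arms close to balanced within each hospital, so differences between hospitals largely cancel from the comparison of arms. A test that pools all patients still counts those differences as random error. If hospitals differ in the outcome, the pooled standard error is larger than the true one, the test rejects less often than its nominal level, and the gain from stratifying is given away.

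The article gives some grounds to expect this for operating time and length of stay. Operations go to designated surgeons, so centre is tied to surgeon. Closure of stoma site leaves the choice of stapled or hand-sewn anastomosis to the surgeon. Conservatism also has a cost in this trial: it aims at preliminary evidence of non-inferiority and assumes no difference in infections, so avoidable imprecision makes both harder to assess.

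**Working it through.** **The plan's own figures.** Sample size uses a 5% hernia rate in both arms, a 5-point margin, α = 0.05 and 80% power. With one-sided α:

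n = (1.645 + 0.842)² × 2 × 0.05 × 0.95 / 0.05² ≈ 235 per group, as stated.

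The drop-out allowance also reproduces: 45 / 0.9 = 50.

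**Continuous outcomes.** Let r be the share of outcome variance explained by centre (the ICC). With arms balanced within centre, the true variance of the difference is about (1 − r) times the one the t test uses. The standard error is then too large by the factor 1/√(1 − r). The true level of a nominal 5% test is 2 × [1 − Φ(1.96/√(1 − r))]. The article gives no value for r, so the range is assumed.

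| r (assumed) | SE used / true SE | True level of the nominal 5% test |
|---|---|---|
| 0.01 | 1.005 | |
| 0.05 | 1.026 | |
| 0.10 | 1.054 | 3.9% |
| 0.20 | 1.118 | 2.8% |

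The formula is for a single measurement compared by a t test. The direction is the same for the Mann-Whitney test, but the size is only indicative.

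**Binary outcomes.** These were simulated: 90 evaluable patients, six centres (15 each, or 35/15/10/10/10/10), blocks of 2, 4 and 6 within centre, no treatment effect, 4,000 runs per scenario. The 5% rate is the article's hernia assumption. The 10% and 20% rates and the between-centre SD on the logit scale are assumptions. The table gives the unadjusted standard error divided by the Mantel-Haenszel (centre-stratified) one.

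| Event rate | No centre effect | Logit SD 0.5 | Logit SD 1.0 |
|---|---|---|---|
| 5% | 0.99 | 1.00 | 1.02 |
| 10% | 0.99 | 1.00 | 1.03 |
| 20% | 0.99 | 1.01 | 1.05-1.06 |

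**What this means for hernia.** Expected events are 90 × 0.05 = 4.5 in total. The standard error of the difference is √(2 × 0.05 × 0.95 / 45) = 0.0459, so the 95% half-width is 1.96 × 4.59 = 9.0 points. A 2% change in the standard error moves that by 0.02 × 9.0 = 0.18 points.

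**Type I error.** Over all scenarios the unadjusted test rejected in 3.2% to 5.3% of runs. Simulation error is about √(0.05 × 0.95 / 4000) = 0.34 points, so 5.3% is compatible with 5%. At logit SD 1.0 the unadjusted test rejected in 3.2-4.9% of runs and the stratified test in 3.4-5.5%.

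**The case against.** The strongest reply is that the loss is hypothetical. The article reports no variation between centres and describes steps that would reduce it: one mesh technique for both devices, one blinded radiologist for all scans, experienced surgeons and a homogeneous patient group. At r of 0.01-0.05 the excess is only 0.5-3%. The trial calls itself a pilot, and its imprecision comes chiefly from 45 per group against the 235 it calculates. On the article's assumptions, non-inferiority power at 45 per group is Φ(0.05/0.0459 − 1.645), about 29%. All of this stands. It limits the size of the point but does not remove the mismatch between design and analysis.

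A second reply is that this is a condensed article and a fuller analysis plan may add centre. That holds for the mixed model, whose fixed effects are not given. It would be too strong to say that every planned comparison excludes centre. It holds less well for the other tests, because the article commits to specific unstratified ones.

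A third reply concerns quality of life. The outcome is improvement over follow-up with a baseline measurement, so a stable shift between centres largely drops out of within-patient change. The table for single measurements does not carry over to it.

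Finally, stratification helps little with rare events. A 15-patient centre at a 5% rate has a chance of 0.95¹⁵ = 46% of no hernia at all, and such a centre adds nothing to a Cochran-Mantel-Haenszel (CMH) test. This is right for hernia.

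**Conclusion.** The point holds as a minor one. Allocation is stratified by centre, and the named t, Mann-Whitney and chi-square or Fisher tests do not use centre. If centre predicts outcome, the tests are conservative. The standard error for operating time and length of stay would be 0.5-3% too large at an assumed ICC of 0.01-0.05, and 5-12% at 0.10-0.20. For infection the excess is 3-6% at assumed rates of 10-20%, and only with strong centre differences (logit SD 1.0). For hernia the change is about −1% to +2%.

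A reader might infer three stronger things that the article does not support:

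- That the standard errors are wrong regardless. This is so only if centre predicts outcome, which is plausible for some endpoints but not documented.
- That the main-endpoint confidence intervals are mis-stated. The hernia intervals in Statistical methods are for the proportion in each group, whereas the calculation here concerns the difference between arms.
- That false-positive risk is raised. The error runs in the conservative direction.

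**What to change.** In Statistical methods, state that between-group comparisons account for centre:

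- **Operating time and length of stay:** a linear model with centre as a fixed effect, or a van Elteren (centre-stratified Wilcoxon) test where a rank test is kept.
- **Quality of life:** centre as a fixed effect in the mixed model, with that model's fixed effects listed.
- **Surgical site infection and, for consistency, hernia:** a Mantel-Haenszel risk difference with a CMH test. A model with centre fixed effects would be unstable with 4 to 5 hernias.
- **Small centres:** a rule set in advance for pooling hospitals that recruit very few patients.

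The cost is a change of wording, since centre is known from randomisation. The statistical price is small. If centre has no effect, intervals for binary outcomes widen by about 1%, and the linear model gives up five degrees of freedom (six centres less one) of the 90 − 2 = 88 available. Centres with no events add nothing to the CMH test.
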